**Table 6-6 Dose Modification Guidelines for Hematologic Toxicities**

| When Platelets:                                                                                                                                                                                                                              | Lenalidomide                                                                                                                                                                                                                                   | Carfilzomib                                                     |                                                                                                                 |
|----------------------------------------------------------------------------------------------------------------------------------------------------------------------------------------------------------------------------------------------|------------------------------------------------------------------------------------------------------------------------------------------------------------------------------------------------------------------------------------------------|-----------------------------------------------------------------|-----------------------------------------------------------------------------------------------------------------|
| Fall to $< 30 \times 10^9/L$                                                                                                                                                                                                                 | 
 
• Hold dose, follow CBC weekly
 
• Hold prophylactic anticoagulation until platelets return to <math>\geq 30 \times 10^9/L</math>
 
• Then resume at 1 dose decrement
 
          | If platelets $10-30 \times 10^9/L$ without evidence of bleeding | 
 
• Hold
 
• With resolution restart at previous dose
 
    |
|                                                                                                                                                                                                                                              |                                                                                                                                                                                                                                                | If evidence of bleeding or platelets $< 10 \times 10^9/L$       | 
 
• Hold
 
• With resolution restart at previous dose
 
    |
| For each subsequent drop to $< 30 \times 10^9/L$                                                                                                                                                                                             | 
 
• Hold dose, follow CBC weekly
 
• Hold prophylactic anticoagulation until platelets return to <math>\geq 30 \times 10^9/L</math>
 
• Then resume at additional dose decrement
 
 | If platelets $10-30 \times 10^9/L$ without evidence of bleeding | 
 
• Hold
 
• With resolution restart at previous dose
 
    |
|                                                                                                                                                                                                                                              |                                                                                                                                                                                                                                                | If evidence of bleeding or platelets $< 10 \times 10^9/L$       | 
 
• Hold
 
• With resolution restart at 1 dose decrement
 
 |
| Grade 4 thrombocytopenia without evidence of bleeding, carfilzomib dosing may occur at the discretion of the treating investigator. However, subjects should receive supportive measures in accordance with institutional guidelines. |                                                                                                                                                                                                                                                |                                                                 |                                                                                                                 |

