Hematologic toxicities were primarily mild or moderate. The thrombocytopenia reported with carfilzomib is cyclical and similar to that reported with bortezomib. The cause and kinetics of the thrombocytopenia following treatment are different from those of standard cytotoxic agents. To maximize the likely benefit of carfilzomib, subjects with thrombocytopenia should be supported as clinically indicated rather than having treatment reduced due to thrombocytopenia.

Of the 36 evaluable patients enrolled in PX-171-002, 20 had MM (Alsina M, 2007). Four MM patients achieved a PR, one of two at the 15 mg/m^2 dose, one of six at the 20 mg/m^2 dose, and two of five at the 27 mg/m^2 dose. The responses have been rapid in onset, beginning in some subjects after 1-2 doses. The duration of response (DOR) ranged from 134 to 392 days. The minimal effective dose was 15 mg/m^2 wherein >80% proteasome inhibition in peripheral blood and mononuclear cells was observed one hour after dosing. The median number of prior therapies for subjects on this trial was five, and responses were seen in subjects who had relapsed from (including some refractory to) bortezomib and/or immunomodulatory agents. Stable disease also occurred in four NHL and five MM subjects, with subjects on therapy for up to 409 days. Such prolonged therapy, at “full” twice-weekly doses, is not possible with bortezomib. These results led to the initiation of two phase 2 studies.

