### **6.3 Study Drug Administration**

#### **6.3.1 Carfilzomib Administration**

Carfilzomib for injection is supplied as a lyophilized parenteral product in single-use vials. The lyophilized product is reconstituted with water for injection to a final carfilzomib concentration of 2.0 mg/mL prior to administration. The dose will be calculated using the subject's actual BSA at baseline. Subjects with a BSA  $> 2.2 \text{ m}^2$  will receive a dose based upon a  $2.2 \text{ m}^2$  BSA. Dose adjustments do not need to be made for weight gains/losses of  $\leq 10\%$ . Subjects with a Body Surface Area (BSA) of greater than  $2.2 \text{ m}^2$  will receive a capped dose of 44 mg of carfilzomib (at the  $20 \text{ mg/m}^2$  dose level), 59.4 mg of carfilzomib (at the  $27 \text{ mg/m}^2$  dose level), or 79.2 (at the  $36 \text{ mg/m}^2$  dose level).

Carfilzomib will be given as an IV infusion over 30 minutes on Days 1, 2, 8, 9, 15 and 16 of Cycles 1- 8 and Days 1, 2, 15 and 16 of Cycles 9-24, and must be administered prior to daratumumab. If the subject has a dedicated line for carfilzomib administration, the line must be flushed with a minimum of 20 mL of normal saline prior to and after drug administration. The dose will be administered at a facility capable of managing hypersensitivity reactions. Subjects will be pre-hydrated with 250mL normal saline or other appropriate IV fluid formulation on cycle 1 Day 1. Other hydration procedures will be optional and per the discretion of the treating investigator. Subjects will remain at the clinic under observation for at least 1 hour following each dose of carfilzomib in Cycle 1 and following the dose on Cycle 2, Day 1. Subjects should be monitored periodically during this period for evidence of fluid overload. Serum chemistry values, including creatinine, must be obtained and reviewed prior to each dose of carfilzomib during Cycles 1 and 2. Refer to [Table 6-8](#) for guidance regarding dose reduction in subjects with compromised renal function.

Doses of carfilzomib may be rescheduled up to 2 days if the scheduled day falls upon a holiday or with approval from the Lead Principal Investigator. If Day 2 of Carfilzomib dosing is delayed (i.e., Day 2, 9, 16) 4 mg of dexamethasone premedication is required to be used prior to second treatment. Missed doses will not be replaced during a cycle. Carfilzomib will be escalated from  $20 \text{ mg/m}^2$  (Cycle 1 Days 1 and 2)

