#### **6.4 Instructions for Initiation of a New Cycle**

A new course of treatment may begin on the scheduled Day 1 of a new cycle if all of the following are met:

- $ANC \geq 1.0 \times 10^9/L$
- Platelet count  $\geq 30 \times 10^9/L$
- Any other study drug-related adverse event must have resolved to Grade 1 or baseline (see Appendix 2)
- Serum uric acid and creatinine concentrations must return to baseline prior to carfilzomib doses during Cycles 1 and 2

If  $ANC < 1.0 \times 10^9/L$  but  $> 0.75 \times 10^9/L$ , the start of a new cycle is at the discretion of the treating investigator

If these conditions are not met on Day 1 of a new cycle, the subject will be evaluated weekly, and a new treatment cycle will not be initiated until the toxicity has resolved, as described above.

If daratumumab, carfilzomib, or lenalidomide, or daratumumab are held for the remainder of the previous cycle or the new cycle is delayed due to residual toxicity on the planned Day 1 of the next cycle, then the new cycle will be started at 1 dose decrement.

If a delay of starting a new cycle is greater than 21 days, the subject should be discontinued from treatment, unless continuing treatment is mutually agreed upon by the site Lead Principal Investigator at the University of Chicago and the co-investigator at the treating institution.

Dexamethasone may be discontinued without the subject discontinuing study treatment.

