## 6.5 Dose-modification guidelines

The following sections and tables summarize dosing modifications of daratumumab, carfilzomib, lenalidomide and dexamethasone to manage possible toxicity. Dose modifications different from those stated in the protocol should be discussed with the Lead Principal Investigator. Administration of daratumumab, carfilzomib and lenalidomide will be discontinued in the event of any other toxicity that, in the opinion of the lead, secondary site, or treating investigator, warrants discontinuation.

In addition to dose reductions, administration of daratumumab, carfilzomib and lenalidomide will be held temporarily in the event of a treatment-related toxicity at the treating investigator's discretion.

Study treatment may be reintroduced if resolution of the event to the baseline value or to  $\leq$  Grade 1 within 21 days; otherwise study drug will be permanently discontinued. Any deviations from this plan must be approved by the Lead Principal Investigator.

All clinically-significant non-hematologic toxicities must be resolved to Grade 1 or baseline.

Individual dose modification of daratumumab is not permitted. Dosing can be delayed to manage daratumumab-related toxicities. Dose de-escalation of daratumumab will be based only on the Data and Safety Monitoring Board (DSMB) recommendation. Dose reduction levels of carfilzomib, lenalidomide and dexamethasone for toxicity management of individual subjects are provided below:

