### **APPENDIX 3: NCI CTCAE VERSION 4.0**

Common Terminology Criteria for Adverse Events (CTCAE) of the  
National Cancer Institute (NCI) v4.0

Publish Date: September 15, 2009

[http://evs.nci.nih.gov/ftp1/CTCAE/CTCAE\\_4.03\\_2010-06-](http://evs.nci.nih.gov/ftp1/CTCAE/CTCAE_4.03_2010-06-14_QuickReference_5x7.pdf)

[14\\_QuickReference\\_5x7.pdf](http://evs.nci.nih.gov/ftp1/CTCAE/CTCAE_4.03_2010-06-14_QuickReference_5x7.pdf)[http://evs.nci.nih.gov/ftp1/CTCAE/CTCAE 4.03 2010-06-14\\_QuickReference\\_5x7.pdf](http://evs.nci.nih.gov/ftp1/CTCAE/CTCAE_4.03_2010-06-14_QuickReference_5x7.pdf)

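### Table 6-6 holds carfilzomib below 10 x10^9/L even without bleeding, but its closing note allows discretionary dosing in non-bleeding Grade 4 thrombocytopenia with no platelet floor

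*Protocol*

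**What the plan says.** Table 6-6 (Protocol, Section 6.5.1.2) gives carfilzomib two conditions once platelets fall below 30 x10^9/L. They are repeated for the first fall and for each later one.

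- Milder condition: "If platelets $10-30 \times 10^9/L$ without evidence of bleeding". The action is hold, then restart at the previous dose, on the first fall and on later ones.
- More severe condition: "If evidence of bleeding or platelets $< 10 \times 10^9/L". The action is hold. Restart is at the previous dose after the first fall and at one dose decrement after any later fall.

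The closing note reads: "Grade 4 thrombocytopenia without evidence of bleeding, carfilzomib dosing may occur at the discretion of the treating investigator". Its only qualifier is that supportive measures be given according to institutional guidelines.

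Three other places bear on the reading. Section 1.3.3 gives the rationale that "subjects with thrombocytopenia should be supported as clinically indicated rather than having treatment reduced due to thrombocytopenia". Section 6.5 says: "Dose modifications different from those stated in the protocol should be discussed with the Lead Principal Investigator". Section 6.4 sets a platelet count of at least 30 x10^9/L among the conditions for starting a cycle on Day 1.

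**The concern.** The more severe row joins its two triggers with an 'or', so a count below 10 x10^9/L calls for a hold whether or not the patient bleeds. The note permits dosing in non-bleeding Grade 4 patients and has no lower limit. For a non-bleeding patient below 10 x10^9/L one instruction says hold and the other says the treating investigator may dose. Nothing in the table ranks them.

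This is a bleeding-safety rule in a study planned at 4 to 6 centers (Section 4.1.1). Without a stated scope, one site can hold and another can dose the same patient, each with support in the same table. The note is also silent on dose level, so a site that doses under it on a later drop cannot tell whether the decrement in that row still applies.

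**Working it through.** The protocol prints no figure to reproduce here. The check sets the rules side by side and asks where their conditions overlap.

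| Platelets (x10^9/L) | Bleeding | Row instruction | Restart, first fall | Restart, later falls | Can the note apply? |
|---|---|---|---|---|---|
| 10-30 | No | Hold | Previous dose | Previous dose | Yes, if the count is Grade 4 |
| Below 10 | No | Hold | Previous dose | One decrement | Yes, if the count is Grade 4 |
| Any below 30 | Yes | Hold | Previous dose | One decrement | No |

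**Where the note meets the severe row.** Let c be the Grade 4 cut-off. The protocol adopts CTCAE v4.0 (Section 8 and Appendix 3) and does not print c, so c is an assumption. For a non-bleeding patient with count p, the severe row applies if p < 10 and the note applies if p < c. Both apply if p < min(10, c).

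- c = 10: both apply for p < 10.
- c = 20: both apply for p < 10.
- c = 25: both apply for p < 10.
- c = 30: both apply for p < 10.

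For any c of 10 or more the overlap is the whole band below 10. This follows directly from the definitions and says nothing about how often such counts occur.

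**Where the note meets the milder row.** For c above 10 the note also reaches the 10-30 cells, from 10 up to c. The band is c - 10 wide: 0, 10, 15 and 20 for the four cut-offs. Those cells also say hold, so the note departs from them too. There, reading it as a deliberate exception is reasonable and agrees with Section 1.3.3.

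**Why below 10 is different.** The table puts a count below 10 in the same cell as bleeding. The note expressly leaves bleeding patients out but does not mention the count grouped with them. On later falls that cell also carries the only platelet-driven reduction of carfilzomib in Table 6-6. The table itself therefore marks 10 x10^9/L as a boundary, and the note crosses it without comment.

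**When it can arise.** Section 6.4 protects Day 1, because a new cycle needs at least 30 x10^9/L. Later carfilzomib days are not protected in that way. Section 6.1.2 schedules hematology on Days 8 and 15 before carfilzomib, so a site could have the count in hand when it faces both instructions.

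**The case against.** The strongest reply is that the note is an ordinary specific exception. It names its condition, its drug, its decision-maker and a condition of use. It is permissive, it sits in a table of guidelines, and it matches the rationale in Section 1.3.3. If it is accepted as an exception to hold at 10-30, consistency suggests accepting it below 10 as well. A floor at 10 would then be a clinical preference that the authors never stated.

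Much of this stands. The exception reading is fair at 10-30 x10^9/L. It does not settle the band below 10, because Section 1.3.3 names no count and the table's own layout treats that band like bleeding. Taking the floor from the table's existing cut is more than a bare preference.

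Three stronger readings are tempting and are not supported:

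- A reader might infer that the note leaves the below-10 trigger with no effect. It does not. Hold remains the default unless the investigator chooses otherwise, and the cut still sets the restart dose after later falls.
- A reader might infer that dosing below 10 clearly calls for the discussion with the Lead Principal Investigator in Section 6.5. That rule concerns modifications different from those in the protocol, and the note is itself in the protocol.
- A reader might count the use of Grade 4 without a printed number as a defect. Reference to CTCAE v4.0 is adequate.

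The practical exposure is also limited. Bleeding patients are excluded and supportive measures are directed. Lenalidomide and prophylactic anticoagulation are held below 30 x10^9/L (Table 6-6). Daratumumab is held at Grade 3 or higher thrombocytopenia (Section 6.5.1.1). Platelet transfusion is allowed (Section 6.2.4). Section 6.3.5 says there will be no new starts, which suggests that few patients remain exposed.

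**Conclusion.** The point holds in limited form. For a non-bleeding patient below 10 x10^9/L on a within-cycle dosing day, Table 6-6 states an unqualified hold and its closing note makes that hold optional, with no floor and no order of precedence. Two of the four carfilzomib cells are affected in this way: the below-10 limb on the first fall and on later falls.

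The conclusion rests on one assumption, that every count below 10 x10^9/L is Grade 4, which is true for any cut-off of 10 or more. The documents give no rate for such counts, so no frequency can be claimed. The sample size, the primary test and all other analyses are untouched. This is a dosing-safety ambiguity worth correcting because the correction is small.

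**What to change.** Reword the note as an exception to the hold for platelets of 10-30 x10^9/L without bleeding, with supportive measures. State that hold applies below 10 x10^9/L or with any bleeding, and that the one-dose decrement on later drops is unchanged. If the Grade 4 cut-off lies below 30 and the sponsor does not want to widen discretion at the upper end, Grade 4 with a count of at least 10 x10^9/L sets the same floor.

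The cost is one reworded note, slightly less investigator discretion, and an occasional lost dose below 10 x10^9/L, since Section 6.3.1 says: "Missed doses will not be replaced during a cycle". The severe row already calls for holding that dose.

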**Table 6-7 Dose Modification Guidelines for Hematologic Toxicities**

| When ANC:                                   | Lenalidomide                                                                                                               | Carfilzomib              |                                                                                 |
|----------------------------------------------------|-----------------------------------------------------------------------------------------------------------------------------------|---------------------------------|---------------------------------------------------------------------------------|
| Fall to $< 0.75 \times 10^9/L$                     | Hold dose, administer myeloid growth factor
Follow CBC weekly
Resume at full dose when $ANC \geq 0.75 \times 10^9/L$        | If ANC $0.5-0.75 \times 10^9/L$ | Continue at full dose                                                           |
|                                                    |                                                                                                                                   | If ANC $< 0.5 \times 10^9/L$    | Hold
Resume at 1 dose decrement when ANC returns to $\geq 0.5 \times 10^9/L$ |
| For each subsequent drop to $< 0.75 \times 10^9/L$ | Hold dose, administer myeloid growth factor
Follow CBC weekly
Resume at 1 dose decrement when $ANC \geq 0.75 \times 10^9/L$ | If ANC $0.5-0.75 \times 10^9/L$ | Continue at full dose                                                           |
|                                                    |                                                                                                                                   | If ANC $< 0.5 \times 10^9/L$    | Hold
Resume at 1 dose decrement when ANC returns to $\geq 0.5 \times 10^9/L$ |

### 6.5.1.3 Non-hematologic Toxicity for Lenalidomide and Carfilzomib

Please refer to **Table 6-8** below for dose modifications for lenalidomide and carfilzomib regarding Non-hematologic toxicities.

**Table 6-8 Dose Modifications for Non-hematologic Toxicity**

| Recommended Action                            |                                                                                                                                                                                                                                       |                                                                                                                                                  |
|------------------------------------------------------|---------------------------------------------------------------------------------------------------------------------------------------------------------------------------------------------------------------------------------------|--------------------------------------------------------------------------------------------------------------------------------------------------|
|                                                      | Lenalidomide                                                                                                                                                                                                                   | Carfilzomib                                                                                                                               |
| Non-Blistering Rash                           |                                                                                                                                                                                                                                       |                                                                                                                                                  |
| Grade 3                                              | 
Hold lenalidomide dose; follow weekly
 
If the toxicity resolves to <math>\leq</math> Grade 1 prior to Day 21 of the current cycle, restart at 1 dose decrement and continue the cycle until Day 21 of the current cycle.
 | 
Hold (if treating investigator's opinion is possibly related to carfilzomib) until <math>\leq</math> Grade 1, reinstitute at current dose
 |
| Grade 4                                              | Discontinue lenalidomide study drug.                                                                                                                                                                                                  | Hold until $\leq$ Grade 1, reinstitute at current dose.                                                                                          |
| Desquamating (blistering) rash – any grade    | Discontinue lenalidomide study drug.                                                                                                                                                                                                  | Hold until $\leq$ Grade 1, reinstitute at current dose.                                                                                          |
| Erythema multiforme <math>\geq</math> Grade 3 | Discontinue lenalidomide study drug.                                                                                                                                                                                                  | Hold until $\leq$ Grade 1, reinstitute at current dose.                                                                                          |
| Sinus bradycardia/ other cardiac arrhythmia   |                                                                                                                                                                                                                                       |                                                                                                                                                  |
| $\leq$ Grade 2                                       | 
Hold lenalidomide dose. Follow at least weekly.
 
If the toxicity resolves to <math>\leq</math> Grade 1 prior to Day 21, restart at 1 dose decrement and continue the cycle until Day 21.
                                 | Hold until $\leq$ Grade 1, reinstitute at current dose.                                                                                          |
| $\geq$ Grade 3                                       | Discontinue lenalidomide study drug                                                                                                                                                                                                   | Hold until $\leq$ Grade 1, reinstitute at current dose.                                                                                          |
| Allergic reaction/hypersensitivity            |                                                                                                                                                                                                                                       |                                                                                                                                                  |

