### **4 INVESTIGATIONAL PLAN**

#### **4.1 Overview of Study Design and Dosing Regimen**

This study will be a multi-center, open-label, phase 2 study, enrolling subjects with newly diagnosed MM requiring systemic chemotherapy. All dosing schedule is based on 28-day cycles. Subjects will receive treatment until disease progression or unacceptable toxicity (whichever occurs first).

Enrolled subjects will initially receive lenalidomide at 25 mg per dose (see below if previously unable to tolerate 25 mg) on Days 1-21. Carfilzomib will be dosed at 20 mg/m^2 on Days 1 and 2 and 36mg/m^2 thereafter (Days 8,9,15, and16). Alternative escalation will be allowed on Cycle 1 if the treating

investigator considers it necessary as follows: 20 mg/m^2 on Days 1 and 2 escalated to 27 mg/m^2 on Days 8 and 9, and then to 36 mg/m^2 on Days 15 and 16. Daratumumab will be administered by subcutaneous injection, provided as a fixed-dosed of 1800 mg and 30,000 units hyaluronidase per 15 mL (120 mg and 2,000 units/mL) for all cycles. The injection will be given by manual push over 3 to 5 minutes in the abdominal SC tissues in left/right locations, alternating between individual doses. Dexamethasone will be dosed at 40 mg PO per week for subjects < 75 years and 20 mg PO per week for subjects ≥ 75 years during Cycles 1-4. Dose modifications will be mandated based on aggressive schedule of dose modification for toxicities as per specific guidelines. Otherwise, patients will continue at their best tolerated dose of lenalidomide on Days 1-21 and their best tolerated dose of carfilzomib on Days 1, 2, 8, 9, 15, 16 in Cycles 1-4 and Days 1, 2, 15, 16 in Cycles 5-8.

All subjects will have monthly clinic visits for disease assessments. Treatment will continue on protocol for up to 24 months or if carfilzomib, lenalidomide and daratumumab are permanently discontinued. If dexamethasone is discontinued due to toxicity, carfilzomib, lenalidomide and daratumumab may be continued if tolerated without dexamethasone. Toxicity will be graded using the National Cancer Institute Common Terminology Criteria for Adverse Events version 4. Patients who complete 24 cycles will then continue single-agent lenalidomide at best tolerated dose (up to 25 mg) in 28-day cycles. This regimen will continue until there is progression of the disease or the toxicities require discontinuation of the drug.

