to 36mg/m^2 (Cycle 1 Days 8, 9, 15, 16 - see below) as long as the subject does not present with cytokine release symptoms (fever, rash, dyspnea, etc.) after Cycle 1 Day 2. If the subject does have concerning symptoms, they will be treated at 27mg/m^2 on Days 8 and 9 before being escalated to 36mg/m^2.

- Cycle 1: 20 mg/m^2 Days 1, 2; 36 mg/m^2 Days 8, 9, 15, 16. Alternatively, intermediate dose escalation (to 27mg/m^2 on Days 8, 9 of Cycle 1) will be allowed at the treating investigator's discretion.
- Cycle 2-8: 36 mg/m^2 (or best tolerated dose) Days 1, 2, 8, 9, 15 and 16
- Cycles 9-24: 36 mg/m^2 (or best tolerated dose) Days 1, 2, 15 and 16

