| Hypertension including Hypertensive Crises                                                                                                                                                                                                                | NA                                                                                                                                                                                                                                                                                                                                | ≥ Grade 3: carfilzomib attribution, hold drug until resolved to ≤ Grade 2. Resume at one level dose reduction                                                                                                                                                                                                                   |
| Heart problems including rapid, strong or irregular heartbeat

Heart attack, reduced blood flow to the heart, abnormal amount of fluid between the heart and lining around the heart, and swelling/irritation of the lining around the heart | NA                                                                                                                                                                                                                                                                                                                                | ≥ Grade 3: carfilzomib attribution, hold drug until resolved to ≤ Grade 1. Resume at one level dose reduction                                                                                                                                                                                                                   |

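### Table 6-8 gives two different carfilzomib restart doses for the same carfilzomib-attributed Grade 3 or higher arrhythmia when treatment restarts within the cycle

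*Protocol*

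**What the plan says.** Two rows of Table 6-8 (Protocol, Section 6.5.1.3) bear on carfilzomib after a rhythm disturbance.

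- The row headed "Sinus bradycardia/ other cardiac arrhythmia" states for Grade 3 or higher, in the carfilzomib column: "Hold until $\leq$ Grade 1, reinstitute at current dose". It sets no attribution condition.
- The row headed "Heart problems including rapid, strong or irregular heartbeat" states in the same column: "≥ Grade 3: carfilzomib attribution, hold drug until resolved to ≤ Grade 1. Resume at one level dose reduction".

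Section 6.4 adds a rule at the cycle boundary. If a study drug is "held for the remainder of the previous cycle or the new cycle is delayed due to residual toxicity", "then the new cycle will be started at 1 dose decrement".

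Table 6-8 is headed as recommended action, but Section 4.1 is firmer: "Dose modifications will be mandated based on aggressive schedule of dose modification for toxicities as per specific guidelines".

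**The concern.** The two rows share the grade threshold (Grade 3 or higher) and the hold criterion (recovery to Grade 1 or lower). They differ in the restart dose: unchanged in one, one level down in the other. A carfilzomib-attributed Grade 3 or higher rapid or irregular rhythm is both a cardiac arrhythmia and an irregular heartbeat, so it meets both descriptions.

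At stake is the re-exposure dose after a severe cardiac event that the investigator has attributed to the drug. In a study of four to six centers, two sites could treat the same event differently, one at the dose that preceded it and one a level lower, and each could point to a row that supports it.

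**Working it through.** **1. The rows side by side (carfilzomib column, Grade 3 or higher)**

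| | Arrhythmia row | Heart-problems row |
|---|---|---|
| Event | sinus bradycardia or any other cardiac arrhythmia | rapid, strong or irregular heartbeat, and other cardiac events |
| Attribution | none required | carfilzomib |
| Hold until | Grade 1 or lower | Grade 1 or lower |
| Restart dose | current dose | one level lower |

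The overlap is a rapid or irregular rhythm of Grade 3 or higher attributed to carfilzomib. Events not attributed to carfilzomib, and pure sinus bradycardia, fall only in the arrhythmia row and are not in conflict.

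**2. Does other text settle it?**

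- Neither Section 6.5 nor the table states an order of precedence.
- The closing rows of Table 6-8 for carfilzomib-related toxicity cover only toxicities not listed elsewhere. This event is already listed, twice.
- Section 6.5 asks that modifications differing from the protocol be discussed with the Lead Principal Investigator. Both restart doses are in the protocol, so neither triggers that step.
- Section 6.4 settles part of it. If carfilzomib is held for the rest of the cycle, or the new cycle is delayed for residual toxicity, the next cycle starts one decrement lower under either row. The rows disagree only if the event resolves in time to restart within the same cycle.

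**3. Size of the disagreement**

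Inputs: Table 6-2 gives 36 mg/m² as the nominal dose and 27 mg/m² as one level down. Section 6.3.1 gives infusions on Days 1, 2, 8, 9, 15 and 16 for Cycles 2–8 and on Days 1, 2, 15 and 16 for Cycles 9–24, and a BSA cap of 2.2 m².

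Per infusion:
- (36 − 27) / 36 = 25% lower.
- At the cap: 2.2 × 36 = 79.2 mg versus 2.2 × 27 = 59.4 mg.

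Cumulative dose = infusions remaining × dose per infusion:

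| Situation | Infusions | Current dose (mg/m²) | One level lower (mg/m²) | Difference (mg/m²) |
|---|---|---|---|---|
| Cycles 2–8, restart Day 8 | 4 | 4 × 36 = 144 | 4 × 27 = 108 | 36 |
| Cycles 2–8, restart Day 15 | 2 | 2 × 36 = 72 | 2 × 27 = 54 | 18 |
| Cycles 9–24, restart Day 15 | 2 | 2 × 36 = 72 | 2 × 27 = 54 | 18 |
| Each later full cycle, Cycles 2–8 | 6 | 6 × 36 = 216 | 6 × 27 = 162 | 54 |
| Each later full cycle, Cycles 9–24 | 4 | 4 × 36 = 144 | 4 × 27 = 108 | 36 |
| Held to end of cycle, or next cycle delayed (per infusion) | – | 27 | 27 | 0 |

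The later-cycle lines assume no further dose change. A patient already at 27 mg/m² would restart at 27 or 20 mg/m². Cycle 1 is left out because its planned dose steps up from 20 to 36 mg/m², so a single contrast does not describe it.

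**The case against.** The best defence is that the table's own pattern shows which row was meant. The rows for hypertension, pericardial effusion, pericarditis and pulmonary hypertension all tie a one-level reduction to carfilzomib attribution, and the closing rows reduce whichever drug is blamed. The arrhythmia row is a catch-all that stops lenalidomide and leaves carfilzomib alone, while the heart-problems row names irregular heartbeat and requires attribution. An investigator who has attributed the event to carfilzomib would naturally use the second row. The case is also narrow: a Grade 3 or higher attributed event must recover in time for a remaining infusion in the same cycle. Weekly multi-institutional safety review (Section 13.6) might catch divergent handling.

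Much of this is fair. The pattern does suggest the intended answer, and the situation will be uncommon. But the reading rests on analogy. Nothing limits the arrhythmia row to events not attributed to carfilzomib, and an arrhythmia of Grade 3 or higher is exactly what that row names. Review after the fact does not tell a site which dose to give. The rows also differ for lenalidomide (discontinue in one, not applicable in the other). That can be read as the second row being silent on lenalidomide, and this point does not depend on it.

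**Conclusion.** The contradiction is real and confined to carfilzomib-attributed Grade 3 or higher rapid or irregular rhythms restarted within the same cycle, together with the doses that follow that restart. There the protocol supports both 36 and 27 mg/m² per infusion at the nominal dose, a 25% difference, or 79.2 versus 59.4 mg at the BSA cap. Outside that case Section 6.4 makes the difference zero.

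The figures assume the patient is at the nominal dose and on the Section 6.3.1 schedule. The protocol gives no rate for these events, so the number of patients affected is unknown. Sample size, error rates, the primary endpoint and discontinuation are not claimed to be affected. The text should be corrected because it governs re-exposure after a severe cardiac event attributed to the drug, and the correction is simple.

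**What to change.** In Table 6-8, in the Grade 3 or higher carfilzomib cell of the arrhythmia row, add: *except carfilzomib-attributed rapid or irregular rhythms, which follow the Heart problems row (resume at one level dose reduction)*. Events not attributed to carfilzomib and pure sinus bradycardia keep the current-dose rule, and the lenalidomide column is unchanged. This agrees with the one-level reduction that Table 6-8 already applies to carfilzomib-related heart failure, pericardial effusion and pericarditis.

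The cost is one clause in one cell, with no effect on sample size, visits or analysis.
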